### Study status and organization

Ewha Womans University Mokdong Hospital is responsible for this trial, and the Institutional Review Board (IRB) of Ewha Womans University Mokdong Hospital approved this research plan, including the written consent form (S2, S3 and S4 File). In addition to Ewha Womans University Mokdong Hospital, at least seven other tertiary hospitals in South Korea are now preparing for IRB approval of each hospital with the same research plan.

This study complied with the fundamental spirit of the clinical trial management standards of the Helsinki Declaration (revised 2013) and the International Conference on Harmonisation of Technical Requirements for Registration of Pharmaceuticals for Human Use–Guidelines for Good Clinical Practice (ICH-GCP). The study was initiated after approval of the IRB in each medical center, and after approval, centers recruited patients and the therapies were administered following the appropriate study protocol and clinical standards.

Patients who met the inclusion criteria and voluntarily agreed to enroll in the study provided written informed consent, which was reviewed and approved by the IRB of each participating hospital after sufficient explanation about the research process. Personal identifiers were kept confidential by the researcher, and the research data was recorded with initials and research subject identification information was coded.

All adverse events reported by the subjects during a 3-month follow-up were reported at meetings between researchers four times a year and evaluated by an independent committee. Interruption of participation was decided when the above adverse reaction was a considerable side effect of the SGLT-2 inhibitors (dapagliflozin and empagliflozin), as informed by the Ministry of Food and Drug Safety, or was a serious adverse event unrelated to causality.

## Discussion

Recently, SGLT-2 inhibitors have been shown to exhibit beneficial effects beyond glucose control. SGLT-2 inhibitors were originally developed as hypoglycemic agents. They target SGLT-2 protein, which is responsible for 90% reabsorption of filtered glucose in the proximal convoluted tubules of the kidneys [35], resulting in diuresis. Previous studies have shown that SGLT-2 inhibitors suppress sympathetic overactivity [36] and oxidative stress [37]. DAPA-HF and EMPEROR-Reduced trial demonstrated that SGLT-2 inhibitors can reduce cardiovascular mortality in patients with HF [14,15]. Considering that AF and CHF are mutual risk factors, we designed a clinical trial based on the rationale that SGLT-2 inhibitors might be able to improve the clinical outcome of AF with DM by establishing the rhythm control of AF.

We will compare the recurrence rate of AF of the two groups after performing AAD administration and hypoglycemic treatment for at least 3 months as a primary outcome and evaluating the degree of rhythm control of AF. Because enlisting patients who were previously diagnosed with DM and whose glucose levels are currently well controlled in the trial can give rise to grave ethical issues, we recruited patients newly diagnosed with AF or DM within 1 year. We decided not to choose any specific SGLT-2 inhibitor agents and their dosage right away; instead, we decided to recommend physicians to utilize the maximum tolerable doses.

Several systemic reviews and meta-analyses have described advantages of catheter ablation over AAD in maintaining sinus rhythm [38–42] and improving the quality of life [43]. The CABANA trial showed that catheter ablation was superior in reducing the recurrence rate of AF compared to the AAD-only therapy [44]. Assuming that catheter ablation will improve the clinical outcome and lower the AF recurrence rate compared to that achieved with the AAD-only treatment in patients with AF and DM, we will add the following procedures after the random assignment of SGLT-2 inhibitors to minimize the bias caused by study protocols: First, the patient takes the assigned medicine for at least 3 months. Second, if AF recurrence is detected and the patient manifests clinical symptoms at follow-up visits, the physician will make a clinical decision on catheter ablation. AF recurrence after ablation (RFA and 4PVI) within a year will be measured by using the established protocol as the primary outcome among patients who have underwent ablation. In this setting, however, comparing the AF burden between the case (SGLT-2 inhibitor) and control (non-SGLT-2 inhibitor) groups at 12 months of trial would disturb the study results. Thus, the recurrence of AF is set as the primary outcome in each step (AAD and ablation).

Previous studies, including DAPA-HF, EMPORER-Reduced, and DECLARE-TIMI 58, have focused on the efficacy of SGLT-2 inhibitors in reducing the risk of adverse cardiovascular events as the primary endpoint in patients with DM, HF, or AF. However, the effects of SGLT-2 inhibitors on arrhythmia, especially AF, were only described by subgroup post-hoc analyses or meta-analyses, so they usually focused on the AF incidence rate and could not analyze other specific properties of AF [16,32,45]. Thus, our trial was advantageous because it allowed the measurement of AF control prospectively in patients with AF and DM.

Very few studies have quantitatively analyzed the AF burden, represented as the percentage of AF time during the monitoring period, because continuous ambulatory monitoring is needed to calculate the exact AF burden [22]. There are some ongoing clinical trials such as DAPA-AF that attempt to quantitatively evaluate the AF burden using cardiac implantable electronic devices (CIED). On the contrary, we plan to measure the AF burden after randomization of SGLT-2 inhibitors, before and after ablation, by utilizing 24-h Holter ECG, which is an excellent choice in terms of accessibility. Furthermore, our study results and information about the population with AF and DM will provide valuable data for subsequent studies in the future.

The LA size and blood level of NT-proBNP are set as the secondary endpoints, as we speculate that SGLT-2 inhibitors will delay the pathophysiologic course of AF. Remodeling of LA by itself acts as an underlying substrate for AF. In addition, progression of AF further deteriorates the LA function and accelerates LA remodeling, thereby continuing the vicious cycle [46,47]. Degree of abnormality of the LA structure and function can be used to determine the positive association with the electrical burden of AF [47]. Therefore, we plan to evaluate the progress of LA remodeling by measuring the degree of LA enlargement, i.e., change in the LA size by utilizing TTE. In addition, considering that NT-proBNP is often increased in AF and shows positive correlation with the clinical severity of AF [27,28], NT-proBNP can be used for assessing the severity of AF. Finally, the quality of life of all patients will be precisely measured.

The trial has some limitations as well. First, it primarily focuses on the effect of SGLT-2 inhibitors in patients newly diagnosed with AF and DM within 1 year. As a result, long-term effects of SGLT-2 inhibitors cannot be analyzed in this trial. Nonetheless, the short-term effects of SGLT-2 inhibitors are meaningful because these inhibitors reduced the incidence of atrial arrhythmia within 1 year compared to that in the control group [32] and the diuretic effect of SGLT-2 inhibitors appeared to be most prominent in first three months of administration only [48]. Second, a certain SGLT-2 inhibitor product is not unified in this trial. Physicians can choose the specific product and the maximum tolerable dose based on their clinical decisions and settings. To control the bias, a subgroup analysis including stratification on products will be conducted as post-hoc analysis.

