## Abstract

SGLT-2 inhibitor, traditionally used for glycemic control, has several beneficial effects that can help manage heart failure (HF). SGLT-2 inhibitors reduce the risk of cardiovascular mortality in patients with HF. As atrial fibrillation (AF) is closely associated with HF and diabetes mellitus (DM) is a risk factor for AF, we assume that SGLT-2 inhibitors will also show therapeutic benefits regarding AF, especially for rhythm control. This trial has a multicenter, prospective, open, blinded endpoint design. It is a 1:1 randomized and controlled study. A total of 716 patients who are newly diagnosed of AF and DM within 1 year will be enrolled from 7 tertiary medical centers. The trial is designed to compare the effects of SGLT-2 inhibitors and other oral hypoglycemic agents on atrial rhythm control in patients with AF and DM. The primary outcome is the recurrence of AF within a year (including post-antiarrhythmic drugs (AAD) or ablation). The secondary outcomes are the ablation rate within a year, change in AF burden, size of the left atrium, NT-proBNP, the AF symptom score, and the quality of life. This trial will prospectively evaluate the effect and safety of SGLT-2 inhibitors on AF rhythm control in patients with DM. It will provide an invaluable dataset on rhythm control in AF with DM for future studies and offer novel information to assist in clinical decisions. (BEYOND trial, ClinicalTrials.gov number: NCT05029115. https://clinicaltrials.gov/ct2/show/NCT05029115).

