## Materials and methods

### Study hypothesis and primary outcome

The primary hypothesis of this study is that the SGLT-2 inhibitor is superior to other oral hypoglycemic medications for rhythm control in patients with AF and DM, diagnosed within the prior year. A step-up treatment will be carried out when the participant’s AF recurs. The recurrence rate of AF will be investigated after performing stepwise rhythm control therapies including anti-arrhythmic drugs (AAD) and ablation. AF is defined as per the 2019 AHA/ACC/HRS Guideline, i.e., irregular R–R intervals (when atrioventricular conduction is present), absence of distinct repeating P waves, and irregular atrial activity [20]. It is checked by 24-h Holter ECG every 3 months and is considered significant when it lasts for > 30 s [21].

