During patient monitoring, if AF recurs and the patient complains of its symptoms, RFA or cryoablation (4PVI) will be performed at the discretion of the physician in accordance with the 2020 ESC [30] 2019 AHA/ACC/HRS guidelines [20] for AF. For patients with ablation, 24-h Holter ECG monitoring every 3 months for an additional year will be performed from that point on. If severe adverse events occur, the patient will be excluded from the study after a committee meeting. The main concern of the review is the recurrence of AF, which is the primary outcome of this trial.

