### Statistical plan, sample size, and power determination

In this study, 716 patients will be enrolled from 7 tertiary medical centers. The sample size was determined based on the primary outcome, i.e., the SGLT-2 inhibitors should show 40% reduction in AF after a year of treatment [32] and 50% of AAD users should step up to the ablation therapy [33,34]. Assuming 10% follow-up loss, the sample size of 716 patients (358 in each group) is expected to achieve 80% power and an alpha-level of 5% to detect the difference. The study is powered to demonstrate the superior additive effect of SGLT-2 inhibitors over other hypoglycemic agents using the Chi square method. AF recurrence rate and ratio of sinus rhythm on 24-h holter EKG will be analyzed using Chi square test, and left atrial size, NT-pro BNP and quality of life (AFEQT) score on 12-month final follow-up will be analyzed by student t-test. Disease-free survival and overall survival during the follow-up period will be calculated using Kaplan-Meier method. Mono-variable and multi-variable cox regression analysis will be used to calculate hazard ratio of SGLT-2 group.

To reduce the selection bias, all subjects will be randomized to allocate the hypoglycemic agents according to random number table. Missing data is planned to be controlled using multiple imputation.

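### The primary outcome is stated in conflicting ways, and one version is a comparison among ablated patients only, which randomisation does not protect

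*Protocol article*

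**What the plan says.** The protocol article describes the primary outcome in four places.

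- Abstract: "The primary outcome is the recurrence of AF within a year (including post-antiarrhythmic drugs (AAD) or ablation". This reads as one outcome over one year.
- Study hypothesis and primary outcome: "The recurrence rate of AF will be investigated after performing stepwise rhythm control therapies". This is compatible with the abstract.
- Discussion, second paragraph: recurrence in the two groups is compared after at least 3 months of AAD and hypoglycemic treatment, and is called a primary outcome.
- Discussion, paragraph on catheter ablation: recurrence within a year after ablation is "measured by using the established protocol as the primary outcome among patients who have underwent ablation", and the paragraph concludes "Thus, the recurrence of AF is set as the primary outcome in each step (AAD and ablation".

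Randomisation allocates only the hypoglycemic agent (Treatment: DM control). On entry to ablation, Follow-up and detection of AF recurrence says "if AF recurs and the patient complains of its symptoms, RFA or cryoablation (4PVI) will be performed at the discretion of the physician". Study design and participants says instead that patients with recurrent AF should step up, and it restarts follow-up at month 0 at the ablation. The design is open label with a blinded endpoint.

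The statistical section names one chi-square test for the recurrence rate. It assumes that "the SGLT-2 inhibitors should show 40% reduction in AF after a year of treatment" and that "50% of AAD users should step up to the ablation therapy", and says that 716 patients "is expected to achieve 80% power and an alpha-level of 5% to detect the difference". It gives no control rate.

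**The concern.** The conflict decides who is an event. A patient who recurs on AAD and then stays in sinus rhythm after ablation is an event at the AAD step and a non-event at the ablation step. The clock differs too: with follow-up restarted at ablation, post-ablation events can fall beyond 12 months from randomisation.

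The more serious problem is the ablated subset. Reaching it requires a recurrence on the allocated drug, and reducing recurrence is what the drug is hypothesised to do. If the hypothesis is right, ablated SGLT-2 patients are those who recurred despite the drug. They would be fewer than the ablated controls and probably have more severe AF. The ablation decision is made by a physician who knows the allocation, and blinding of the endpoint does not reach that decision. The protocol also lists the ablation rate as a secondary outcome that the drug may change, yet it conditions a primary outcome on ablation. A real benefit could be masked there, or harm suggested where there is none.

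**Working it through.** **1. The stated sample size.** Inputs from the statistical section: 40% reduction, alpha 5%, power 80%, 10% loss, 50% step-up, 358 per arm. Evaluable per arm: 358 × 0.9 = 322. The control rate is not stated, so 716 cannot be reproduced from stated inputs alone. Solving for it with the two-sided pooled formula

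n = [1.96√(2p̄(1−p̄)) + 0.84√(p₁(1−p₁) + p₂(1−p₂))]² / (p₁−p₂)²

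gives:

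| Reading | Assumed rates | n per arm | Inflation | Total |
|---|---|---|---|---|
| Ablated half only | 35% vs 21% | 161 | 161/0.5 = 322; 322/0.9 = 358 | 716 |
| All randomised | 20.3% vs 12.2% | 323 | 323/0.9 = 359 | 718 |
| 50% taken as control rate | 50% vs 30% | 93 | 93/0.9 = 104 | 208 |

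The first matches exactly and the second nearly, so the figure does not show which population it rests on.

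**2. Size of the ablated subset.** If 50% of controls and, after a 40% reduction, 30% of SGLT-2 patients reach ablation, the subset is 322 × 0.5 = 161 vs 322 × 0.3 ≈ 97. At an assumed 35% vs 21%, power there is 67%, against 80% with 161 in each arm.

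**3. Direction and size of the selection bias (illustration).** Assumptions, none given by the protocol:

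- AAD-phase recurrence is 50% (control) and 30% (SGLT-2), and every recurrence is ablated.
- Severity U is normal(0,1). The logit of recurrence is a constant plus bU in both phases.
- The post-ablation constant is set so that ablated controls recur at 35%.
- The drug has no effect after ablation.

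The SGLT-2 rate is then the average of the same post-ablation risk over the severity of those who recurred on SGLT-2. The rejection column is the two-sided 5% test at 161 vs 97. The last column multiplies the SGLT-2 post-ablation risk by 0.60.

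| b (log-odds per SD) | Control | SGLT-2 | Bias | Rejection with no drug effect | True RR 0.60 appears as |
|---|---|---|---|---|---|
| 0.5 | 35% | 36.0% | +1.0 points | 5.4% | 0.62 |
| 1.0 | 35% | 38.5% | +3.5 points | 8.9% | 0.66 |
| 1.5 | 35% | 41.3% | +6.3 points | 17.6% | 0.71 |

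Almost all of these rejections go against SGLT-2. At b = 1.0, about 8.3% indicate harm and 0.6% benefit.

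A second set of assumptions (30% post-ablation recurrence overall, shared severity explaining 30%, 50% or 70% of the variance) gives 38% vs 43%, 44% vs 52% and 51% vs 63% (control vs SGLT-2), with rejection in 11%, 24% and 52% of trials. The direction is the same, but the size depends heavily on the assumptions.

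**4. Multiplicity, conditional on an either-may-win rule.** Two independent tests at 5%: 1 − 0.95² = 9.75% two-sided. Counting only false superiority: 1 − 0.975² = 4.9%, against 2.5% for one test.

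**5. Power for one primary in all randomised patients.** With 322 evaluable per arm, a 40% reduction and 5% two-sided:

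| Assumed control rate | 20% | 25% | 30% | 35% |
|---|---|---|---|---|
| Power | 79% | 89% | 95% | 98% |

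**The case against.** A reader might infer that the trial tests its primary hypothesis twice at 5% and so inflates the chance of a false superiority claim. The article does not support that. It states one alpha and one chi-square test, assigns 5% to neither step separately, and says neither that either step may win nor that both must. If both had to succeed, there would be no inflation. An alpha rule may also sit in an analysis plan that is not shown. The 9.75% is therefore conditional, and it counts rejections in both directions.

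Nor does the selection bias add to that error. In the illustration it runs against SGLT-2 and makes false superiority in the subset rarer than 2.5%.

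It is also fair to say that the size of the bias is not identified. The 35% post-ablation rate and the severity link are assumed. The 50% in the protocol is a step-up share, not a control recurrence rate. Ablating every recurrence ignores the symptom and physician conditions.

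Two further readings go too far. The section on the hypothesis agrees with the abstract, so the conflict is between those two and the Discussion. And although 716 fits the ablated half exactly, an all-patient control rate near 20% fits almost as well, so the article does not show that the sample size rests on the subset.

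What the objection leaves untouched is the text. The Discussion gives primary status to each step and restricts the second to ablated patients. Reading the abstract as one composite in all randomised patients would be reasonable on its own, but the Discussion contradicts it.

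**Conclusion.** The point holds, and it should be settled before the analysis. The primary outcome is defined inconsistently, and followed as written the Discussion makes a primary comparison in a group formed after randomisation. The comparisons in all randomised patients, including the AAD step, remain randomised, so the defect is confined to the ablation step and to the uncertainty over which outcome is primary.

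If the drug lowers AAD-phase recurrence and AF severity is shared across phases, the likely bias is against SGLT-2. Under the first set of assumptions it is about 1 to 6 points, with a true risk ratio of 0.60 appearing as 0.62 to 0.71; other assumptions give larger values. Multiplicity is a secondary and conditional matter: up to 9.75% two-sided, or about 4.9% for false superiority, only if either step alone could establish superiority at an undivided 5%.

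**What to change.** - Name one primary outcome: AF recurrence longer than 30 s within 12 months of randomisation, in all randomised patients, by allocated arm. Count an AAD-phase recurrence as an event whatever happens after ablation. State whether recurrences in the first 3 months count. Test it once at 5%.
- Make post-ablation recurrence a secondary outcome, labelled descriptive and non-randomised.
- Say how the primary differs from AF-free survival, which is already the first secondary outcome and would otherwise largely duplicate it.
- Align the Abstract, the section on the hypothesis and primary outcome, and both Discussion paragraphs. Reconcile the two descriptions of how patients enter ablation.
- State the control rate and restate the power behind 716 for all randomised patients, including what the 50% step-up share then contributes.

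The 3-monthly Holter schedule already supplies the data. The cost is that the post-ablation comparison loses primary status and the sample-size justification must be rewritten. At an assumed control rate of 20% or more, 716 patients still give about 79% power or better; below that, power drops (65% at 15%).

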• Any disease that limits life expectancy to under 1 year • Subject for another clinical trial within the past 2 months • Under 18 years old or over 80 years • Pregnant women • Lactating women • Drug abuser • Type 2 DM treated by recombinant insulin • Diagnosis of Type 1 DM, MODY, or secondary DM • HbA1c ≥ 12% or HbA1c < 6.5% at diagnosis • Previous treatment with any SGLT-2 inhibitor • Renal dysfunction (eGFR-CKD-EPI < 30 mL/min/1.73 m^2^) • Chronic cystitis and/or recurrent genitourinary tract infections (3 or more in the last year) • Unexplained hematuria at baseline study • Systolic BP > 180 mmHg or diastolic BP > 100 mmHg at baseline study • Systolic BP < 95 mmHg at baseline study • Previous treatment with AF ablation • Acute cardiovascular event [e.g., stroke, acute coronary syndrome (ACS), revascularization, decompensated HF, sustained ventricular tachycardia, return of spontaneous circulation (ROSC)] <8 weeks prior to baseline study • Severe valvular disease or have prosthetic valve • Treatment with chronic oral steroid (>30 consecutive days) at a dose equivalent to oral prednisolone ≥ 10 mg/d, within the past 1 month • History of any malignancy within 5 years • Clinically profound hepatic dysfunction • Clinically uncontrolled thyroid dysfunction • Patients incapable of completing the trial because of any severe medical condition by clinical decision • Patients with poor compliance (defined as 80–120%), except for reasonable situations judged by physician

DM, diabetes mellitus; MODY, maturity onset diabetes of the young; EPI, epidemiology collaboration; BP, blood pressure; AF, atrial fibrillation; HF, heart failure.

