### Treatment: DM control (allocation)

The subjects will receive oral hypoglycemic agents for glucose control; the type of agents will be determined by randomization. Patients using SGLT-2 inhibitors to control their serum glucose will be specified as the case group, while those using other hypoglycemic agents (e.g., metformin, meglitinides, sulfonylureas, DPP-4 inhibitors, GLP-1 receptor agonists, α-glucosidase inhibitors, and thiazolidinediones) to control their serum glucose will be classified as the control group. The number, type, and dosage of the agents will be individualized at the discretion of the physician in accordance with the 2021 ADA guidelines [31], considering factors such as the kidney function, age, and cardiovascular status.

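### Stratifying on the SGLT-2 product received cannot control the bias from physician choice of product and dose; a subgroup by pre-recorded intended product would be valid for product, though not for dose

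*Protocol article*

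**What the plan says.** On allocation, the section Treatment: DM control says that "the type of agents will be determined by randomization". The two types are SGLT-2 inhibitors and other hypoglycaemic agents, and patients who use the other agents "to control their serum glucose will be classified as the control group". Within this, "The number, type, and dosage of the agents will be individualized at the discretion of the physician", with renal function, age and cardiovascular condition among the considerations.

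The Discussion adds that "We decided not to choose any specific SGLT-2 inhibitor agents and their dosage right away". Among the limitations it states that "Physicians can choose the specific product and the maximum tolerable dose based on their clinical decisions and settings". The remedy follows directly: "To control the bias, a subgroup analysis including stratification on products will be conducted as post-hoc analysis".

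Two further facts matter. Study design and participants describes treatment as open with blinded endpoint assessment. Table 4 excludes "Previous treatment with any SGLT-2 inhibitor".

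**The concern.** The remedy is stated as a property of the analysis: stratifying on product is said to control the bias that free choice of product and dose brings in. Stratification controls a factor only if the factor can be defined in both arms and is not itself a consequence of allocation. Product received meets neither condition.

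At stake are the product-level conclusions. If physicians tend to give one product to patients at higher risk of AF recurrence, that product will look less effective than another with the same effect, and the article would present the contrast as bias-controlled.

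**Working it through.** The plan gives no figure for this analysis, so there is none to reproduce. The design reasoning comes first, then an illustration of size.

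**1. Which comparisons exist.** Randomisation fixes the class. The physician chooses the product within the SGLT-2 arm. The article does not say in so many words that this happens after allocation, but it follows from class-level randomisation, open treatment and a product not fixed in advance. Controls take other agents, and earlier SGLT-2 use is excluded, so no control patient has a product value, even at baseline. What remains is product A users against all controls, product B users against all controls, or A users against B users. None of these is randomised.

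**2. Possible size.** One input is from the article: the 40% reduction in the statistical plan, taken as a risk ratio of 0.60. The rest is assumed, because the article gives no control recurrence rate, no product mix and no link between product choice and prognosis:
- two products, each with a true risk ratio of 0.60;
- a prognostic factor in half the patients, with control risk 0.35 without it and 0.65 with it, so 0.5 × 0.35 + 0.5 × 0.65 = 0.50 overall;
- product choice that depends on the factor.

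Let f be the share of a product's users who have the factor. Their underlying risk is 0.35 + 0.30f, and the apparent ratio against all controls is 0.60 × (0.35 + 0.30f) / 0.50.

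| A given to patients without / with the factor | f for A, B | Underlying risk A, B | Apparent ratio A, B |
|---|---|---|---|
| 50% / 50% | 0.5, 0.5 | 0.50, 0.50 | 0.600, 0.600 |
| 60% / 40% | 0.4, 0.6 | 0.47, 0.53 | 0.564, 0.636 |
| 70% / 30% | 0.3, 0.7 | 0.44, 0.56 | 0.528, 0.672 |
| 80% / 20% | 0.2, 0.8 | 0.41, 0.59 | 0.492, 0.708 |

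A simulation of 4,000,000 patients agrees within simulation error: 0.566 and 0.637, 0.529 and 0.674, 0.494 and 0.708 for the last three rows.

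**3. The class comparison.** In the 60/40 row, SGLT-2 recurrence is 0.5 × (0.60 × 0.47) + 0.5 × (0.60 × 0.53) = 0.30, and 0.30 / 0.50 = 0.60. The other rows give the same. Free product choice does not bias the comparison as allocated.

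**4. Intended product recorded before allocation.** Controls in stratum A now have the same underlying risk as SGLT-2 patients in stratum A. In the 60/40 row, 0.282 / 0.47 = 0.60 and 0.318 / 0.53 = 0.60. The same holds in every row.

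**5. What that does not repair.**
- *Dose.* A maximum tolerable dose is known only after treatment starts. Assume 80% of patients without the factor and 40% with it reach full dose. Then f = 0.4 / 1.2 = 0.333 at full dose and 0.6 / 0.8 = 0.75 at reduced dose. The ratios against all controls are 0.60 × 0.45 / 0.50 = 0.54 and 0.60 × 0.575 / 0.50 = 0.69, with 0.60 true for both. Within intended-product strata (70/30 selection) the simulation still gives about 0.55 at full dose and 0.66 to 0.71 at reduced dose.
- *Analysis by product received.* If 10% of patients without the factor and 30% with it receive the other product, comparing product received with controls for whom that product was intended gives 0.64 and 0.58.

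**6. Precision.** With 10% loss, 358 × 0.9 is about 322 evaluable per arm, and a stratum holding half has 161 per arm. Two-sided power for the arm comparison in that stratum is about 50% for 20% against 12%, and 96% for 50% against 30% (both control rates assumed). The difference between strata is estimated less precisely still.

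**The case against.** The strongest reply is that this is one sentence among the limitations, about an analysis the authors themselves call post hoc, while the primary hypothesis and the randomisation concern the class. The article does not say that product groups will be set against the whole control arm, or without adjustment. It plans multivariable Cox regression, and fuller detail may lie in a document not shown. Relabelling alone would remove the misstatement.

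Much of this stands. The stakes are confined to an exploratory analysis, the inputs in the illustration are assumed, and deleting the claim is the minimum remedy. But the point concerns something the article asserts, not detail it omits. No Cox model can stratify controls on a product they do not have. Covariate adjustment would give an observational comparison that depends on having measured the reasons for choice.

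Three stronger readings are tempting and not supported:
- *That the main result is biased.* It is not, if patients are analysed as allocated (step 3). Free choice only makes the SGLT-2 arm heterogeneous.
- *That the trial would find one product effective and another not.* Every apparent ratio in the table is well below 1. The illustration shows a false difference in size only.
- *That the article contradicts itself on products.* Study status and organization refers to a "considerable side effect of the SGLT-2 inhibitors (dapagliflozin and empagliflozin" when it describes interruption of participation. Naming two products is compatible with the Discussion's statement that the product is not unified.

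**Conclusion.** The concern holds for the product-stratified analysis and the claim attached to it. With only the class randomised and product defined in one arm, the planned stratification cannot control selection by product or by dose. Under the assumed inputs, two identical products with a true ratio of 0.60 would appear as about 0.56 and 0.64 under mild selection and 0.49 and 0.71 under strong selection. With no selection on prognosis the distortion is nil, and the article does not allow the actual degree to be judged. A reader might also infer that recording the intended product solves the whole problem. It solves the product subgroup only: dose subgroups remain confounded.

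**What to change.** - In the Discussion, delete the statement that the product analysis controls bias and call the analysis exploratory.
- For patients still to be randomised, have the physician record, before the allocation is revealed and in both arms, which SGLT-2 product would be used if the patient were allocated to that class.
- Replace the planned analysis with SGLT-2 against control within intended-product strata, plus an arm-by-intended-product interaction. Analyse by intended product, not by product received.
- State three limits: the analysis does not address dose; a difference between strata compares effects in differently selected patients and is not a randomised comparison of products; patients already randomised will lack the field and cannot enter it.

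The cost is one field at randomisation and a few sentences in the analysis section. Some patients will receive a product other than the one intended, so each stratum estimates the effect in patients for whom that product was intended. The article says in the past tense that centres recruited after approval, so the number without the field is unknown and may not be zero. If the field is judged not worth adding, the first change alone still corrects the misstatement.
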